# A phase 2 study of stereotactic body radiation therapy for squamous cell carcinoma of the head and neck (SHINE): a single arm clinical trial protocol

**DOI:** 10.1186/s12885-023-10807-4

**Published:** 2023-04-26

**Keywords:** Stereotactic radiation therapy, Head and neck cancer, Squamous cell carcinoma, Radiation therapy

## Abstract

**Background:**

Cancers of the head and neck region are often characterized by locally advanced, non-metastatic disease. Standard treatments for advanced cervico-facial cancers of the skin or primary head and neck squamous cell carcinoma (HNSCC) include combinations of surgery, radiation and chemotherapy, which are associated with high rates of acute toxicity and complications. Stereotactic body radiotherapy (SBRT) has been shown to be a promising modality of treatment for this patient population in retrospective studies; to our knowledge, there are no prospective clinical studies evaluating the safety and efficacy of SBRT in these patients.

**Methods:**

This phase 2, single institution, single arm study aims to evaluate response rates to SBRT in older age patients with locally advanced HNSCC for whom primary surgery is not recommended or performed. The intervention is SBRT 45 Gy in 5 fractions given every 3–4 days. Toxicity, quality of life and patient outcomes will be recorded regularly up to 24 months after completion of SBRT.

**Discussion:**

For this patient population, SBRT may offer a shorter and more effective treatment than the current standard of care palliative regimens. If the study demonstrates that SBRT is safe and effective, then this may lead to randomized studies comparing conventional radiotherapy to SBRT for selected head and neck cancer patients.

**Trial registration:**

ClinicalTrials.gov Identifier: NCT04435938.  Date registered: June 17, 2020.

**Supplementary Information:**

The online version contains supplementary material available at 10.1186/s12885-023-10807-4.

## Background

Cancers of the head and neck region account for approximately 4% of all new cancer cases. Primary skin cancers are the most common malignancy diagnosed in North America with the majority of tumours arising in the cervico-facial region [1, 2]. Together, these tumours comprise a high burden of illness and are often characterized by locally advanced, non-metastatic disease.

Determining the optimal treatment for individual patients with advanced cervico-facial cancers of the skin or primary head and neck squamous cell carcinoma (HNSCC) is clinically challenging; standard treatments include combinations of surgery, radiation and chemotherapy, all of which are associated with high rates of acute toxicity and complications [3]. A meta-analysis of randomized controlled trials did not demonstrate benefit with concurrent chemotherapy in patients over the age of 70 or with performance status ≥ 2, and it is recognized that the high burden of medical co-morbidities in HNSCC is associated with poorer prognosis [4-6]. Some patients without distant metastases may be deemed to have ‘incurable’ disease due to very advanced tumours, recurrence, severe medical co-morbidities or frailty that prohibit the use of standard surgery, general anaesthetic and/or radiotherapy over 6–7 weeks [7-9].

When conventional surgery and/or radiotherapy are not recommended by the multi-disciplinary team then patients may be treated with shorter, hypo-fractionated radiotherapy with the goal of symptom relief and local control but at the cost of a lower biological dose. Investigators at the Juravinski Cancer Centre published retrospective results from the ‘0–7-21’ regimen using 24 Gy / 3 fractions which was well tolerated and provided temporary symptom relief in 82% of patients but reported 6 month progression free survival of 39% within the irradiated field [7]; a phase 2 study of previously untreated HNSCC patients deemed to have incurable disease used up to 42 Gy/12 fractions and demonstrated similar rates of initial response and symptom relief but a short progression free survival duration of 3.1 months [8]. Stevens et al. reported an institutional experience of palliative radiotherapy in newly diagnosed head and neck cancer patients who were deemed to have incurable disease and received a wide range of dose/fractionation regimens. The median radiation dose was 50 Gy and between 57–82% of patients were reported to have any radiological, clinical or symptomatic response to treatment [9]. In these three studies, the patients were older with median ages of 71, 73, and 77 years- and median survival was short 5.2, 5.7 and 6.2 months [7-9].

With respect to squamous cell carcinoma (SCC) of the skin, there is limited evidence to guide treatment in patients with unresectable or medically inoperable disease, particularly in the head and neck region [10]. There is a need for prospective data on non-surgical treatment options for frail older adults which improve efficacy while limiting the treatment burden [11].

SBRT can limit the number of treatments while delivering a higher, potentially curative dose. An international consortium of 15 high volume cancer centres reported on a survey of practices using SBRT for head and neck cancers [12]. There was heterogeneity in the indications, techniques and doses reported by various institutions. The most common indication was in the setting of recurrent disease and reported doses were in the range of 35–50 Gy in 3–5 fractions. Several institutions reported 1–2 year local control rates of 65–90% with SBRT [12-15] and acceptable levels of toxicity. To our knowledge, there are no prospective clinical studies evaluating tumour response, toxicity and quality of life in previously unirradiated patients.

The goal of the current study is to prospectively evaluate tumour response, toxicity and patient quality of life in patients with HNSCC undergoing SBRT.

## Study objectives

### Primary objective

To evaluate the tumour response rate of squamous cell carcinoma of the head and neck following stereotactic body radiotherapy (SBRT).

### Secondary objectives:

To measure acute and late toxicity rates associated with SBRT treatments to the head and neck regionTo measure patient reported outcomes including quality of life and specific symptoms associated with head and neck cancer and SBRT treatmentTo determine local control, locoregional control and progression free survival following SBRT

## Study design

A phase 2, single arm study to evaluate response rate to SBRT in patients with locally advanced squamous cell carcinoma of the head and neck region, including primary skin SCC (Scheme I).

**Scheme I Sch1:**
[figure not shown]
Study Schema**.** Abbreviations: SCC = squamous cell carcinoma; SBRT = stereotactic body radiotherapy

## Study population

### Inclusion criteria.

Age >  = 60 yearsHistologically confirmed diagnosis of squamous cell carcinoma of the head and neck region including primary skin SCC; (malignant cells with suspicious/likely SCC will be considered for study if repeat biopsy is not feasible)Clinical stage ≥ T2, or any T-stage with N1-N3 disease, M0 or MxMeasurable tumour present in the head and neck region on clinical examination and/or imaging at time of study enrollmentAll patients will be assessed by a multi-disciplinary, head and neck oncology team with no systemic therapy being recommended at the time of enrollmentPrimary surgery not recommended/performed due to any of the following:Unresectable disease and/or borderline
resectableMedically inoperable / deemed high risk for
post-operative morbidity/mortality by surgical teamPatient declined surgeryDeemed not to be a candidate for standard fractionation radiotherapy due to poor performance status and/or medical co-morbidities and/or advanced stage diseaseEastern Co-operative Oncology Group (ECOG) Performance Status ≤ 3

### Exclusion criteria.

Life expectancy ≤ 3 monthsChemotherapy or other systemic cancer therapy within 3 months prior to HN SBRTBasal cell carcinoma, Merkel cell, malignant melanoma, adenocarcinoma are excludedHN surgery within 6 months prior to HN SBRT (excision under local anaesthesia is acceptable)Prior radiation treatment to the head and neck region (prior radiotherapy to the skin for non-melanoma skin cancer and deemed to have no risk of overlap with the current field are eligible)Synchronous or recent cancer diagnosis not including the index cancer (other cancers treated curatively with no evidence of disease for >  = 3 years, or other non-melanoma skin cancers treated with no evidence of disease for >  = 6 months are eligible)Confirmed or known distant metastatic diseaseSerious non-malignant disease that precludes definitive radiation treatment (e.g. severe cases of scleroderma, systemic lupus erythematosus, rheumatoid arthritis)Unable to provide written, informed consent or complete QoL questionnaires and assessments required on the studyUnable to lie flat for 60 min in order to have radiation planning and treatmentUnable to attend radiation planning and therapy, as well as follow-up care and assessmentsUnable to provide written, informed consent

## Pretreatment evaluation and subject enrollment

Following the multi-disciplinary consultation including a head and neck surgeon and radiation oncologist, patients who meet the inclusion criteria will be screened and approached for eligibility assessment and potential study enrollment. Written informed consent is obtained for all eligible patients prior to commencing any study related procedures.

All potentially eligible and consenting patients who do not meet the exclusion criteria will have a CT simulation of head and neck region. Based on our experience in the head and neck clinic, less than 10% of patients in this population will be unable to tolerate the CT with head and neck immobilization. Patients who cannot tolerate the simulation procedure with immobilization will be treated off study.

## Baseline assessment

Complete history and physical examination; multi-disciplinary clinic consultThe baseline assessment includes the collection of patient demographics, height, weight, tumour characteristics (disease site, histolology, TNM staging), prior treatments received, reasons for not having surgery and/or conventional fractionated radiotherapy.Charlson Co-morbidity Index (CCI) and ECOG performance StatusQuality of Life Questionnaire: Functional Assessment of Cancer Therapy-Head and Neck (FACT HN) [16].Vulnerability and Frailty Assessments: Vulnerable Elders Survey 13 (VES13) [17] and Geriatric 8 (G8) [18].No routine bloodwork is required for the current studyDiagnostic CT and/or MRI of the head and neck region with IV contrast as per the usual standard of care will be performed. Patients who have contra-indications to CT/MRI must have a clinically measurable skin lesion to be included.For skin tumours, clinical measurements using calipers and clinical photographs will be recorded as per the usual standard of care

## Study treatment

### Stereotactic Body Radiation Therapy (SBRT)

#### Radiation dose

The dose prescribed in the study will be 45 Gy in 5 fractions, delivered once every 3–4 days, such that treatment is completed within 15 days (e.g. treatment given on Monday/Thursday/Mon/Thurs/Mon). Exceptions: treatment duration of up to 18 days will be allowed to account for cancer centre closures and unforeseen patient issues.

#### Simulation and planning

Radiation planning, simulation and treatment will adhere to the principles of SBRT described within the ASTRO-ACR and JCC practice guidelines [19]. Positioning and immobilization will be determined by the treating radiation oncologist and must allow the patient to be comfortable during the SBRT procedure. It is expected that all cases will utilize a thermoplastic immobilizing mask unless the patient is unable to tolerate the setup. Skin surface wires, clinical markings and clinical photographs will be used as per the usual standard of care for patients with tumours involving the skin. A planning CT scan will be performed for treatment planning using 1.5 mm image slice thickness. MR simulation will be performed when feasible, at the discretion of the treating radiation oncologist and fused with the CT sim images. IV contrast for CT and/or MR simulation will be used unless there are contraindications to contrast dye.

#### Target delineation and treatment of the primary tumour

The prescription dose GTV45 volume will be contoured on neck / soft tissue windows by the treating radiation oncologist to include all tumour regions and abnormal tissue on CT and MRI simulation images. No high dose CTV expansion will be used. A 5 mm expansion from GTV45 will be used to determine the high dose PTV45.

A microscopic dose CTV volume of 27 Gy/5 fractions will be contoured for the primary tumour. CTV27 will consist of the GTV with an expansion of 10 mm to encompass microscopic disease excluding air and anatomic boundaries such as bone and adjacent intact muscle planes. An additional 5 mm expansion will be used to determine the microscopic dose PTV27.

#### Target delineation and treatment of nodal disease

There will be no elective nodal radiotherapy for patients with stage N0 disease. Patients with regional nodal disease (biopsy proven or radiologically short axis ≥ 1 cm or with malignant features) will undergo treatment to encompass all involved nodes. A volume defined as “GTV45_nodal_” will be contoured by the radiation oncologist on neck/soft tissue windows to encompass all abnormal regional lymph nodes. No high dose CTV45_nodal_ volume will be used. A 5 mm PTV volumetric expansion from GTV45_nodal_ will be used to determine PTV45_nodal._

A microscopic dose CTV volume of 27 Gy will be contoured for nodal volumes. CTV27_nodal_ will consist of the nodal GTV with an expansion of 2 cm to encompass microscopic nodal disease excluding air and anatomic barriers such as lung, bone, muscle unless there is suspicion of direct invasion. A 5 mm expansion will be used to determine the PTV27_nodal_ contour.

#### Radiation treatment technique

Volumetric Modified Arc Therapy (VMAT), Intensity Modulated Radiotherapy (IMRT) or Cyberknife robotic radiosurgery are preferred treatment techniques for this study and will be determined by the treating radiation oncologist, in consultation with the medical physicist and radiation therapist.

Cone beam CT will be used for daily image guidance and matched to the primary tumour as well as organs at risk. Radiation treatment is to start within 14 days of the CT/MR simulation.

#### Radiation dose constraints (Additional file 2)

Radiation prescription to targets will be such that the following criteria are met:GTV45 V100 > 95% and PTV45 V95 > 95%PTV45 Dmax < 115% and mean dose < 105%PTV45 V107 < 8%

#### Organs at risk – dose volume constraints (Additional file 2)

SBRT of the head and neck region is a relatively recent treatment approach. Therefore, radiation limits for the current study are based on a published survey of current HN SBRT practices at 15 international institutions as well as published experiences from other disease sites [12].

### Treatment verification

Verification of linear accelerator treatments will be performed daily using cone beam CT (CBCT) prior to each fraction of treatment. CBCT will be matched to the high dose GTV and adjacent soft tissue and bony structures. Patients treated with robotic radiosurgery will require real-time tumor tracking.

### Treatment review

Patients will be seen once weekly during or following treatment in review clinic to monitor any adverse events, as per the usual standard of care.

## Radiation therapy quality assurance

All cases on study will undergo a real-time review prior to the start of treatment by study radiation review committee, consisting of a radiation oncologist, medical physicist and radiation therapist (planner) to confirm that the plan meets the target delineation, target coverage and organ at risk constraints described in the protocol. In addition, all plans will be reviewed at standard head and neck disease site group weekly quality assurance rounds.

## Adjuvant systemic supportive therapy

### Permitted concomitant medication and therapy

Standard supportive treatments including patients` regular medications, antibiotics, analgesics, inhalers. No concurrent or adjuvant chemotherapy/immunotherapy is permitted. Palliative chemotherapy/immunotherapy is permitted three months after completion of the study treatment if indicated due to locoregional progression or at any time if the patient develops distant metastatic disease; currently the majority of patients in this study population do not receive palliative systemic therapy due to limited response rates, toxicity, co-morbidities and patient preference.

### Prohibited concomitant medication and therapy

Any non-standard systemic treatment as an adjuvant treatment.

### Supportive therapy

There is no planned additional supportive therapy during protocol treatment. However, therapy used to aid in subject comfort and symptoms during treatment (pain medications, inhalers) are permitted. Standard of care during head and neck radiotherapy typically includes skin moisturizer or topical antibiotics, sodium bicarbonate mouthwash or medicated mouthwashes, and analgesics as required.

## Evaluations during and after radiotherapy

### Assessment and evaluations during treatment: (Additional file 1).

Once per week during the treatment the patient will undergo the standard review clinic with the nursing staff and radiation oncologist to assess acute toxicity. This is the usual standard of care.The research associate will administer and record acute toxicity, and quality of life questionnaires once during radiotherapy, at the time of the 4^th^ or 5^th^ treatment.

### Post treatment assessment and evaluations: (Additional file 1).

The patient will be seen at four assessments following completion of therapy at 6 weeks, and then at 3, 6, 12 months. Follow-up imaging with CT and/or MRI of the head and neck region will be performed 10–12 weeks after the last radiation treatment as per the usual standard of care. Toxicity, quality of life questionnaires, ECOG performance status assessment, will be administered at each follow-up visit and the tumour dimensions from clinical examination and/or any diagnostic imaging will be recorded. Any additional follow-up investigations/imaging will be done at the discretion of the oncology team. Regular follow-up after the 12 month visit will continue as per the usual standard of care. A chart review and data extraction will be performed by the clinical research associate to assess local control and progression free survival 2 years after completion of the treatment.

### Early permanent discontinuation of radiotherapy.

All definitive treatment discontinuation should be recorded by the Investigator, along with reasons for discontinuation.

#### Criteria for early permanent discontinuation of radiotherapy

Study treatment will be stopped prematurely and permanently if any of the following events occur or are diagnosed:Severe acute toxicity requiring hospitalizationSignificant change in clinical status due to comorbid illness such that the subject is unable to continue with protocol treatment.

### Follow-up after early permanent discontinuation of radiotherapy.

Subjects who meet the criteria for early permanent discontinuation of radiotherapy and do not receive further protocol treatment will continue to be followed for cancer recurrence. Efforts should be made to continue the follow-up schedule for survival unless the subject withdraws their consent from collection of data beyond the point of withdrawal from the protocol treatment.

## Cancer recurrence and other cancer events

At the time of first cancer recurrence, all subjects will be reassessed, undergo clinical examination, and the site of recurrence will be recorded as will treatment at time of recurrence. Re-staging investigations including chest x-ray, CBC, liver function tests, bone scan, and liver ultrasound or chest /abdominal CT will be done at the discretion of the most responsible physician and the oncology team. Treatment of recurrence is at the discretion of the treating oncologist and may include further radiotherapy, chemotherapy, targeted therapy, surgery, or supportive care. Subjects will continue to be followed for the primary outcome. Cancer recurrence and survival data pertaining to the secondary outcome (refer to Sect. 11) will be collected.

## Study outcomes

### Primary outcome

The primary outcome is tumour response rate (complete or partial response) as defined by RECIST 1.1 criteria [20]. Tumour response is the best overall response across all time points during the study period – up to 24 months after completion of SBRT.

### Secondary outcomes.

#### Toxicity

Acute (during and up to 3 months from the end of treatment) and late (after 3 months) adverse effects secondary to SBRT treatment will be graded according to the Common Terminology Criteria for Adverse Events (CTCAE v5.0) scale [21]. We expect less than thirty percent of patients will develop grade 3 or higher toxicity based on SBRT literature.

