### Statistical analysis

Tumour response and control will be reported based on all available clinical/imaging measurements and classified using the RECIST criteria. Adverse events will be summarized using the NCI-CTCAE. The number of patients with grade ≥ 2 toxicity will be reported. Any grade 4–5 toxicity or adverse event on the study will be reported. Baseline demographics, tumour characteristics and reason for no surgical management will be reported with descriptive statistics. The baseline Charlson Comorbidities Index, VES13 and G8 scores will be summarized to assess the study population for vulnerability/frailty. Quality of life and symptom scores will be assessed to identify the severity and duration of changes to these scores during and after SBRT. Exact confidence intervals will be constructed for outcomes of interest and statistical significance will be defined as a two-sided α ≤ 0.05 for all analyses other than the primary outcome. No interpolation will occur for any missing information.

All patients who receive at least one protocol defined treatment will be included in all analyses. Any patient registered to this study who does not receive protocol defined treatment will be described, including reasons for not receiving treatment, but will not be included in further analyses.

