## Safety monitoring plan

Patients treated with HN SBRT on this study are anticipated to have significant frailty and co-morbidities that preclude surgery, conventional radiotherapy and systemic therapy. Studies involving a similar patient population at JCC and other centres reported median survival between 5–6 months and deem the treatment intent to be palliative [9-11]. Head and Neck cancer patients in Ontario are known to have a high rate of emergency room visits and hospitalizations [3]. Therefore, it is likely and expected that some patients may be admitted to hospital or die during the duration of the study; this may be caused by complications due to the tumour and associated treatments or for reasons unrelated to the cancer diagnosis.

A data safety monitoring committee (DSMC) consisting of at least two radiation oncologists who are not co-investigators in the study will review all grade 4 or 5 (severe) adverse events. Any severe adverse events will be classified as definitely related, possibly related or not related to the study intervention. Toxicity will be reviewed by the DSMC on a q6 monthly basis or more frequently if unexpected toxicity is observed. If grade 5 toxicity is observed in more than 10% of patients, the protocol will be amended to a lower radiation dose (40 Gy) for REB review, or the study may be closed.

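### The abstract promises toxicity recording to 24 months but scheduled collection stops at 12, and the grade 3+ rate that carries the stated expectation is not among the named toxicity summaries

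*Protocol article*

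**What the plan says.** **Length of recording.** The abstract (Methods) states: "Toxicity, quality of life and patient outcomes will be recorded regularly up to 24 months after completion of SBRT". The section on post-treatment assessment sets the visits: "The patient will be seen at four assessments following completion of therapy at 6 weeks, and then at 3, 6, 12 months". It ties toxicity to those visits: "Toxicity, quality of life questionnaires, ECOG performance status assessment, will be administered at each follow-up visit". After the 12-month visit it names usual care and a chart review "to assess local control and progression free survival 2 years after completion of the treatment". The Quality of Life section also ends at 12 months. The Toxicity section applies CTCAE v5.0 and splits events by time, in a sentence that opens "Acute (during and up to 3 months from the end of treatment) and late (after 3 months) adverse effects secondary to SBRT treatment will be"; it gives the late period no upper limit.

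**Grade cut-offs.** The Toxicity section adds: "We expect less than thirty percent of patients will develop grade 3 or higher toxicity based on SBRT literature". The Statistical analysis section first provides a CTCAE summary of adverse events without a grade limit. It then names the number of patients with grade 2 or higher, and says: "Any grade 4–5 toxicity or adverse event on the study will be reported". It provides exact confidence intervals for outcomes of interest and a two-sided 0.05 level for everything except the primary outcome. In the Safety monitoring plan, the committee "will review all grade 4 or 5 (severe) adverse events". It also reviews toxicity every six months with no grade limit, and grade 5 toxicity in more than 10% of patients triggers an amendment or possible closure.

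**The concern.** The article gives two data-collection plans that cannot both be right. A site that follows the visit schedule will have no planned toxicity record for the second year, although the abstract tells readers that one exists. An analysis plan cannot repair this later, because it cannot analyse data that were not collected. Acute and late toxicity rates are a secondary objective, and the patients concerned are the longest survivors, in whom late effects of a high dose per fraction matter most.

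The second part is smaller. The one rate that the protocol puts an expectation on is grade 3 or higher, yet the two cut-offs it names lie on either side of it. The grade 2+ count is an upper bound for the grade 3+ count and the grade 4–5 count a lower bound; neither gives it. The abstract and the Discussion both make a safe and effective result the condition for randomised studies, so the toxicity estimate that will be read against the expectation should be fixed in advance rather than picked from several cut-offs once the data are seen.

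**Working it through.** **1. The collection windows side by side**

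| Item | Abstract | Body of the article |
|---|---|---|
| Toxicity | to 24 months | 6 weeks, 3, 6 and 12 months |
| Quality of life | to 24 months | last at 12 months |
| 2-year chart review | not mentioned | local control and progression-free survival |
| Late toxicity period | not defined | starts after 3 months, no end given |

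Toxicity and quality of life both end 12 months short of the abstract's statement. Nothing in the body schedules toxicity between 12 and 24 months.

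**2. How many patients the gap may touch**

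Inputs: maximum n = 38 (Sample size section); median survival of 5 to 6 months in similar patients (Safety monitoring plan) and 5.2, 5.7 and 6.2 months (Background). The exponential curve is my assumption: S(t) = 0.5^(t/m), with m the median.

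- m = 5: S(12) = 0.189, 38 × 0.189 = 7.2 patients; S(24) = 0.036, 1.4 patients.
- m = 6.2: S(12) = 0.261, 9.9 patients; S(24) = 0.068, 2.6 patients.

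So about 7 to 10 patients would enter the uncovered period and about 1 to 3 would reach its end. By the same formula, 25 to 27 of 38 would be alive at 3 months, which is roughly the number at risk for late toxicity.

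**3. What a grade 3+ proportion would show**

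The article attaches no calculation to the 30% figure, so there is none to reproduce. Its only calculated figures belong to the response design (6/11, then 26/38; 60% against 80%). The exact two-stage binomial gives α = 0.0970, β = 0.0958 and a stage I stopping probability of 0.4672, matching the stated 0.097, 0.096 and 0.467. I therefore take n = 38 and n = 11 as given.

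Exact (Clopper–Pearson) 95% limits for x events in n: lower = the 0.025 quantile of Beta(x, n − x + 1); upper = the 0.975 quantile of Beta(x + 1, n − x).

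| Events | Observed | 95% CI |
|---|---|---|
| 5/38 | 13.2% | 4.4–28.1% |
| 6/38 | 15.8% | 6.0–31.3% |
| 11/38 | 28.9% | 15.4–45.9% |
| 0/11 | 0% | 0–28.5% |
| 1/11 | 9.1% | 0.2–41.3% |

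At n = 38 the largest count whose upper limit lies below 30% is 5. At n = 11, if the trial stops after stage I, only zero events would do.

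Chance of seeing 5 or fewer events among 38, P(X ≤ 5) with X binomial: 0.825 if the true rate is 10%, 0.485 at 15%, 0.200 at 20% and 0.060 at 25%. A true rate moderately below 30% would usually not be distinguished from 30%.

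**The case against.** A reader might infer that the expectation on grade 3+ toxicity cannot be tested, because only grade 2+ and grade 4–5 events are analysed. The documents do not support that. The CTCAE summary in the Statistical analysis section has no grade limit, adverse effects of SBRT are graded and divided into acute and late, and exact intervals are already provided for. A grade 3+ proportion can be computed from data collected to 12 months.

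A reader might also take the 30% figure as the trial's only safety benchmark. It is not: the Safety monitoring plan has its own trigger on grade 5 toxicity and a six-monthly toxicity review of all grades. The 30% is worded as an expectation, with no error rate or power behind it. Reading it as a hypothesis, and setting 6/38 as a pass mark at a one-sided 5% level, would conflict with the two-sided 0.05 of the Statistical analysis section, under which 6/38 does not exclude 30%.

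Three further points can be made for the plan. Which grade cut-off gets its own table row is often left to the analysis plan, which is not shown. The promise to report any grade 4–5 event on the study has no 12-month limit, so severe late events could still come to light. Additional file 1, cited for the assessments, is not shown either. These reduce the weight of the concern. They do not remove the conflict between the abstract and the body, nor supply a scheduled toxicity assessment after 12 months.

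**Conclusion.** The concern holds in two limited parts. First, the abstract's 24 months contradicts the 12-month schedule for both toxicity and quality of life, and late toxicity in months 12 to 24 has no planned collection. This is worth correcting because it concerns a secondary outcome and the correction is cheap. Its likely reach is small, about 7 to 10 of 38 patients alive at 12 months. That range rests on exponential survival and on medians from earlier palliative series; it would be larger if SBRT prolongs survival, as the investigators hope.

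Second, the grade 3+ proportion is not named although it is the rate with a stated expectation. This is a gap in specification, not in data: the rate is derivable to 12 months. Any estimate will be imprecise, so an observed value just under 30% should not be presented as showing that the rate is below 30%. The sample size and the response design are unaffected.

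**What to change.** 1. Add SBRT-related late toxicity of grade 3 or higher to the 2-year chart extraction that is already planned. Label it as chart-abstracted and possibly under-recorded, and report it apart from events graded at study visits.
2. Correct the abstract to 12 months for quality of life. If toxicity is not added to the extraction, correct it to 12 months for toxicity as well.
3. In the Statistical analysis section, name the proportion of patients whose worst grade is 3 or higher, acute and late separately, with the exact two-sided 95% interval. State the number at risk for the late proportion.
4. Describe that proportion against the 30% expectation without a pass/fail rule, and note that with 38 patients only 5 or fewer events would exclude 30%.

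The cost is wording and a few extraction fields, with no change to sample size or visits. The downside is that toxicity taken from charts may be incomplete.
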